### Implementation {16c}

Random allocation of patients to one of the treatment arms will be done by a third party who is not involved in any of the trial procedures.

Patients will be enrolled in the trial by the local PIs, and after communicating the pseudonymized data of a new trial participant, the third party for randomization will assign the participant at hand to one of both treatment arms (cfr. supra).

## Assignment of interventions: blinding

### Who will be blinded {17a}

Trial participants will be blinded and, as mentioned above, randomization of patients will be concealed for the treating surgeon up until 1 week preoperatively.

Blinding of outcome assessors and data analysts was considered, but we decided against this due to practical considerations.

### Procedure for unblinding if needed {17b}

Upon patient’s request, unblinding is allowed after termination of the trial.

In case of any unforeseen medical emergency requiring unblinding of the trial participant, unblinding will be allowed as well.

Unblinding will occur through face-to-face contact between the trial participant and the local PI who may then reveal the exact surgical technique that was performed.

## Data collection and management

### Plans for assessment and collection of outcomes {18a}

FFS after 3, 12, and 24 months will be assessed by urethroscopy using a flexible 16-Fr cystoscope. Not being able to pass this flexible cystoscope past the area of reconstruction will be logged as a failure.

Changes in functional outcome 3, 12, and 24 months after the operation will be assessed with validated questionnaires, as mentioned above. The scores on these questionnaires will be compared with the baseline questionnaire every patient has to fill in preoperatively. A short list of these questionnaires can be found hereafter:
Change in erectile function: IIEF-5 questionnaireChange in ejaculatory function: MSHQ-EjD short form questionnaireChange in LUTS: ICIQ-MLUTS module and Peeling’s voiding pictureChange in urinary incontinence: ICIQ-UI short form questionnaireChange in quality of life: EQ-5D-3L questionnaire and EQ-VASPostoperative patient satisfaction: 2 separate questions.

Change in Qmax will be assessed by uroflowmetry at 3, 12, and 24 months postoperatively and will be compared to the preoperative Qmax.

Postoperative complications will be assessed by the treating surgeon through thorough history taking and physical examination at the 3-month follow-up moment. Surgical complications will be logged and categorized according to the Clavien-Dindo classification system [15, 16].

Every local PI of every participating center will receive an electronic document stipulating how to assess the aforementioned outcome variables and how to enter these data in the online data registry (cr. infra). The follow-up of patients within this trial is comparable to the follow-up of urethroplasty patients outside the context of a clinical trial, and therefore, no specific training for outcome assessors is foreseen.

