### Outcomes {12}

Primary end-point
To show that FFS after vsAR is non-inferior to tAR after 24 months of follow-up.❖ Failure is defined as the inability to pass a 16-Fr flexible cystoscope through the reconstructed area without damaging the urethral mucosa. This anatomical definition of failure was chosen based on the fact that it has—to the best of our knowledge—the highest sensitivity and specificity to detect stricture recurrence after urethroplasty. In our opinion, this end-point leaves little to no room for interpretation, whereas a functional definition of failure (“need for re-intervention”) might be strongly influenced by the treating physician (e.g., physicians who personally favor technique A over B might be more reluctant to offer redo surgery to this group compared to patients treated with technique B, thus introducing the biased result that A would be better than B because fewer patients have to be re-operated during the follow-up period).❖ The non-inferiority limit, *d*, was set at 10%. This non-inferiority limit was chosen based on experts’ opinion, 5 patients’ opinion and a round-the-table consensus discussion.❖ The fact that failure after AR usually occurs within the first years after surgery serves as the rationale behind the follow-up interval of 24 months in this study [13].

Secondary end-points

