#### Analysis of the secondary end-points

Postoperative changes in erectile function, ejaculatory function, LUTS, urinary incontinence, and quality of life will be analyzed by comparing the scores of the postoperative questionnaires with the scores of the preoperative questionnaires. For every participant, the 3-, 12-, and 24-month follow-up questionnaire scores will be compared to the respective preoperative questionnaire scores. Differences in scores will be logged for the 3-, 12-, and 24-month follow-up moment, and for each of these time-points, the median (interquartile range (IQR)) change in scores will be assessed for vsAR and tAR. Median (IQR) change in scores will be compared between vsAR and tAR using a two-sided Mann-Whitney *U* test at the 20% significance level.

As regards de novo postoperative worsening of erectile function, defined as a decrease of ≥ 5 points on the postoperative IIEF-5 questionnaire compared to the preoperative IIEF-5 questionnaire, a two-sided Fisher’s exact test at the 20% significance level will be used to compare vsAR and tAR at the 3-, 12-, and 24-month follow-up moment.

Postoperative patient satisfaction will be assessed at the 3-, 12-, and 24-month follow-up moment. For each time-point, the proportion of satisfied patients will be compared between vsAR and tAR using a two-sided Fisher’s exact test at the 20% significance level.

Postoperative change in Qmax will be compared between vsAR and tAR at the 3-, 12-, and 24-month follow-up moment using a two-sided Mann-Whitney *U* test at the 20% significance level.

Postoperative complications will be compared between vsAR and tAR using a two-sided Fisher-Freeman-Halton test at the 20% significance level.

Note that for all secondary end-points, participants will be censored at the moment they undergo a subsequent urethral treatment (dilation, urethrotomy, urethroplasty, or urinary diversion).

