### Methods in analysis to handle protocol non-adherence and any statistical methods to handle missing data {20c}

Participant retention, protocol adherence, and minimization of missing data will be promoted by scheduling every foreseen follow-up moment (10 days, 3 months, 12 months, and 24 months postoperatively) in advance, ideally at the moment of inclusion or at the moment of discharge from the hospital. If patients do not show up at the foreseen follow-up moment and do not reschedule, they will be invited for a new appointment by telephone or e-mail.

In case of drop-out, patients will be contacted by the local PI and the reason for drop-out will be logged qualitatively. In case of no further contact with the participant at hand, “unknown reason for drop-out” will be logged. These participants will be censored at the moment of latest follow-up.

In case of protocol non-adherence, the reason for this will be logged qualitatively by the local PI.

Missing or incorrect data will be detected by software programs and will be reported transparently in the publication of trial results.

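### The rule for logging the primary failure omits the mucosal-damage element of its definition, and re-treatment has no stated place in the primary analysis, so failures can be under-counted

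*Protocol article*

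**What the plan says.** **Definition.** Outcomes {12} states: "Failure is defined as the inability to pass a 16-Fr flexible cystoscope through the reconstructed area without damaging the urethral mucosa". The abstract and Objectives {7} give the same definition. A scope that goes through but damages the mucosa is a failure under it.

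**Logging rule.** Plans for assessment and collection of outcomes {18a} first fixes the times: "FFS after 3, 12, and 24 months will be assessed by urethroscopy using a flexible 16-Fr cystoscope". It then says: "Not being able to pass this flexible cystoscope past the area of reconstruction will be logged as a failure". The mucosal-damage condition is absent.

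**Re-treatment.** Outcomes {12} explains why re-intervention was not chosen as the definition of failure: the anatomical end-point is said to leave little room for interpretation, "whereas a functional definition of failure (“need for re-intervention”) might be strongly influenced by the treating physician". The section on the secondary end-points says that "for all secondary end-points, participants will be censored at the moment they undergo a subsequent urethral treatment", and lists dilation, urethrotomy, urethroplasty and urinary diversion. The section on the primary analysis has no counterpart. Section 20c deals with drop-outs only: "These participants will be censored at the moment of latest follow-up".

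**Blinding.** Section 17a: "Blinding of outcome assessors and data analysts was considered, but we decided against this due to practical considerations".

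**The concern.** The trial has one primary end-point, and the article words it in two ways that classify the same patient differently. The difference lies in whether the mucosa was damaged, which is the element that most needs judgement, and the person judging knows the arm.

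The second gap concerns a foreseeable event. The authors anticipated further urethral treatment and wrote a rule for it, but limited that rule to the secondary end-points. A recurrence that is dilated or incised between visits may let the scope pass at the next visit.

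Both gaps can turn a true failure into a recorded success. In a non-inferiority comparison of absolute failure-free proportions, failures lost in equal shares from both arms shrink the observed difference and its variance, and both effects make the margin easier to meet. With about two failures expected per arm, small changes in classification carry weight.

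**Working it through.** **1. The two rules side by side**

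| Scope result | Abstract, Objectives {7}, Outcomes {12} | Section 18a, read literally |
|---|---|---|
| Passes, mucosa intact | failure-free | failure-free |
| Passes, mucosa damaged | failure | not logged as failure |
| Does not pass | failure | failure |

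The rules differ in the middle row only.

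**2. Re-treatment between visits**

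The scheduled scopes leave gaps of 12 − 3 = 9 and 24 − 12 = 12 months. Take a man re-treated within a gap with no failed scope logged before. The secondary rule does not reach the primary analysis, the drop-out rule does not apply because he stays in follow-up, and the primary analysis section is silent. If the scope passes at his next visit, nothing shown prevents his being recorded as failure-free. Nothing shown says he must be, either.

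**3. The plan's own sample size**

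Inputs from Sample size {14}: success 95.4% (tAR) and 95.3% (vsAR), margin 10 points, one-sided alpha 0.10, power 0.80.

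n = (z₀.₉₀ + z₀.₈₀)² × [0.954×0.046 + 0.953×0.047] / (0.10 − 0.001)²
= (1.2816 + 0.8416)² × 0.088675 / 0.009801 = 40.8, so 41 per arm, as stated.

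Expected failures at n = 41 are 41 × 0.046 = 1.9 (tAR) and 41 × 0.047 = 1.9 (vsAR).

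**4. What missed failures would do at the margin**

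True failure rates are set at 4.6% (tAR) and 14.6% (vsAR), a difference of exactly 10 points. Let m_t and m_v be the shares of failures missed in each arm. These shares are assumptions; the document gives none. The recorded rates are 4.6%(1 − m_t) and 14.6%(1 − m_v), so

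observed difference = 10 − 14.6 m_v + 4.6 m_t points.

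It narrows unless m_t exceeds 14.6/4.6 = 3.2 times m_v.

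For every pair of failure counts at 41 per arm, compute the upper limit for excess vsAR failures and sum the binomial probabilities of the pairs where it is below 10%. The Newcombe limit is (p_v − p_t) + √[(u_v − p_v)² + (p_t − l_t)²], where u_v and l_t are 80% Wilson limits (z = 1.2816). The Wald (unpooled) limit is shown for comparison.

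| Failures missed (assumed) | Newcombe 80% | Wald 80% |
|---|---|---|
| none | 9.1% | 11.9% |
| 10% in both arms | 11.7% | 15.9% |
| 20% in both arms | 15.3% | 21.1% |
| 30% in both arms | 20.0% | 27.9% |
| 20% in vsAR only | 18.9% | – |
| 20% in tAR only | 6.9% | – |

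This treats follow-up as complete. The planned Kaplan-Meier interval with censoring will differ somewhat, but the ordering does not depend on that.

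**5. How near one patient is to the verdict**

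With 2 of 41 tAR failures:

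- Wald, 3 vsAR failures: 0.0244 + 1.2816 × √(0.0732×0.9268/41 + 0.0488×0.9512/41) = 0.0920, a lower limit of −9.2% for the difference in failure-free survival. With 4 failures it is −12.2%. The verdict changes between 3 and 4.
- Newcombe, 3 vsAR failures: 0.0244 + √[(0.1433 − 0.0732)² + (0.0488 − 0.0205)²] = 0.1000 (0.10002 unrounded), so −10.0% and just outside the margin. With 2 failures it is −6.9%. The verdict changes between 2 and 3.

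The tipping point depends on the interval, but under either method one reclassified patient can decide the result.

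**The case against.** The strongest reply is that 18a is shorthand. Its sentence names one event that is logged as failure and does not say that it is the only one. The full definition appears three times elsewhere, and local investigators are to receive a separate instruction document that is not shown. That lowers confidence but does not remove the discrepancy: 18a is the section that governs what is recorded, and the unseen document cannot be assumed to settle it.

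On re-treatment, the gap is read from silence. The definition is not tied to scheduled visits, so a failed scope at an unscheduled visit would meet it. In a Kaplan-Meier analysis a failure once logged is not undone by a later pass. The gap is thus confined to men re-treated before any failed scope was recorded. The full protocol or an analysis plan may close it. All of this stands. What remains is that the article states a rule and expressly limits it to the secondary end-points.

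The authors also had a reason to avoid re-intervention as the end-point: treating physicians may favour one technique. Counting re-treatment lets some of that influence back in, since men who would still pass the scope could be added as failures, perhaps unequally by arm. This is a real cost and calls for a sensitivity analysis. It is not a reason to leave re-treatments that actually occur without a rule.

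Finally, a verdict that turns on one patient reflects the few expected events, not the wording. That is correct; the fragility only shows why the wording matters.

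**Conclusion.** The point holds in a limited form. The definition and the logging rule differ for a scope that passes with damage, and the primary analysis has no stated handling of re-treatment. Failures **can** therefore be under-counted.

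A reader might infer three stronger things that the document does not support:

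- That failures **are** under-counted. This would require 18a to override the definition, and re-treated men to be scored as successes. Neither is stated.
- That any error must favour non-inferiority. That is so when misses are similar in both arms or heavier in vsAR. It reverses when they fall mainly on tAR, and unblinded assessment does not exclude that.
- That the size of the effect is known. The rise from 9.1% to between 11.7% and 20.0% rests on assumed shares of 10% to 30% missed in both arms, true rates exactly at the margin, complete follow-up and the Newcombe interval.

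The sample size is unaffected. Severity: should-fix. Confidence: moderate.

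**What to change.** 1. In 18a and on the data entry form, use the definition from Outcomes {12}. Record one of three results at each scope (passed without damage, passed with damage, not passed) and count the last two as failure.
2. Keep the anatomical definition as the end-point. Add that dilation, urethrotomy, urethroplasty or diversion for the reconstructed segment before 24 months, with no failure logged earlier, counts as a primary failure at the date of that treatment. Censoring at re-treatment would be a poor substitute, because it would be informative and would remove likely failures.
3. Report the cystoscopy-only definition as a sensitivity analysis.

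The cost is one form item and a few sentences, with no change in sample size. The downside is some physician influence through the decision to re-treat; comparing the two definitions will show whether it matters.

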### Plans to promote participant retention and complete follow-up {18b}

Participant retention will be promoted by scheduling every foreseen follow-up moment (10 days, 3 months, 12 months, and 24 months postoperatively) in advance, ideally at the moment of inclusion or at the moment of discharge from the hospital. If patients do not show up at the foreseen follow-up moment and do not reschedule, they will be invited for a new appointment by telephone or e-mail.

### Data management {19}

The local PIs of the participating centers will enter all required data individually in a firewall protected online data registry which complies with the guidelines of good clinical practice. Access to this online data registry is only possible upon invitation by the central PI or the trial coordinator and by use of a unique, center-specific password. All data will be stored in a central IBM SPSS database which is protected by an institutional firewall system. All data, entered and stored, will be pseudonymized to comply with current privacy regulations. Local PIs will have access to the data of their own patients enrolled in this trial. The central PI and the trial coordinator will have access to all data. Before the start of recruitment, every local PI of every participating center will receive an electronic document including a list of variables that will be collected and thorough instructions on how to enter data. A manual bimonthly data check will be performed by the trial coordinator to optimize data quality.

### Confidentiality {27}

Data entry and communication about trial participants will be pseudonymized to guarantee confidentiality, before, during, and after the trial. Pseudonymized patient data will only be accessible for members of the research team.

### Plans for collection, laboratory evaluation, and storage of biological specimens for genetic or molecular analysis in this trial/future use {33}

Not applicable as no biological specimens will be collected as part of this trial.

## Statistical methods

### Statistical methods for primary and secondary outcomes {20a}

ITT analyses will be used for all end-points.

#### Analysis of the primary end-point

Kaplan-Meier curves for FFS will be plotted with the corresponding log-log 80% CIs for vsAR and tAR.

Non-inferiority of vsAR versus tAR in terms of FFS at 24 months will be concluded when the lower limit of the 80% CI for the difference in FFS probability at 24 months does not exceed − 10%. Note that this analysis does not take into account the nesting of patients within centers, which may affect the estimated standard errors.

To take into account the clustering of patients within centers, a marginal Cox proportional hazards model can be fitted (using the cluster function from the “survival” package in R software) which will give a robust estimation of the variance. The lower limit of the 80% CI for the hazard ratio can be transformed into a limit of survival difference at 24 months, assuming an exponential distribution of failure-free survival times [*S*(*t*) = exp.{−*λt*}].

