### Sample size {14}

Power analysis and sample size calculation for this non-inferiority trial were performed using an online software package:

Sealed Envelope Ltd. 2012. Power calculator for binary outcome non-inferiority trial. [Online] Available from: https://www.sealedenvelope.com/power/binary-noninferior/ [Accessed Mon Apr 162,018].

Different scenarios were simulated, of which the results are discussed below. In all scenarios, 10% was considered the non-inferiority limit, *d*, as mentioned above.

- Scenario 1: power 0.80; estimated success in control group (tAR): 95.4%; estimated success in experimental group (vsAR): 95.3%; for different one-sided alphas:

❖ Alpha 0.025: 72 patients per arm

❖ Alpha 0.05: 56 patients per arm

❖ Alpha 0.10: 41 patients per arm

- Scenario 2: power 0.80; estimated success in control group (tAR): 95.4%; estimated success in experimental group (vsAR): 95.4%; for different one-sided alphas:

❖ Alpha 0.025: 69 patients per arm

❖ Alpha 0.05: 55 patients per arm

❖ Alpha 0.10: 40 patients per arm

- Scenario 3: power 0.80; estimated success in control group (tAR): 97.4%; estimated success in experimental group (vsAR): 93%; for different one-sided alphas:

❖ Alpha 0.025: 227 patients per arm

❖ Alpha 0.05: 179 patients per arm

❖ Alpha 0.10: 131 patients per arm

The numbers that were put in the above simulations are based on an in-home analysis of patients who underwent anastomotic repair at Ghent University Hospital between 2000 and 2017. Herein the FFS at 24 months for vsAR and tAR were 95.3% (standard deviation (SD), 2.3%) and 95.4% (SD, 2.0%) respectively. These exact results are represented in scenario 1. Scenario 2 represents a situation in which the surgical outcome would be exactly the same for vsAR and tAR. Scenario 3 represents a less favorable situation in which vsAR has a 24 m-FFS of 93% (95.3% − SD) and tAR has a 24 m-FFS of 97.4 (95.4% + SD).

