In every scenario, the power was set at 0.80, according to the guidelines for designing a phase II trial [21]. The results for different alphas are displayed above. Usually, a non-inferiority trial demands a significance level, alpha, of 0.025 as these trials only look at one boundary of the classic two-sided 95% confidence interval (CI) [22]. However, these conditions often lead to (sometimes unreasonably) high sample size calculations requiring excessive financing and recruitment. As a solution, researchers often design a phase II trial that allows for more coincidence and thus a trial with a higher significance level, alpha. Rubinstein et al. reported alpha values of 0.10 and 0.20 to be allowed in a phase II trial [21]. Considering the fact that a non-inferiority trial relies on one-sided testing, we believe a one-sided significance level, alpha, of 0.10 is allowed and most feasible.

Considering all of the above, a scenario in which the power is set at 0.80, the one-sided significance level, alpha, is set at 0.10, the estimated success in control group is set at 95.4%, and the estimated success in experimental group is set at 95.3% was found most realistic and feasible. Considering this and accounting for a realistic drop-out of 20% (experience based), it was estimated that each arm has to consist of 50 patients, resulting in a total sample size of 100 patients.

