### Methods for additional analyses (e.g., subgroup analyses) {20b}

Interaction tests for FFS were considered for traumatic versus non-traumatic stricture etiology and for primary versus secondary procedures. However, the rule of thumb says that at least 10 failures are needed per degree of freedom included in the model. Allowing for a modification of the effect of procedure by stricture etiology for instance would imply adding 3 degrees of freedom to the model (technique, center, and stricture etiology). This would lead to overfitting, which means the obtained results might not be reproducible in other samples. We will refrain from generalizing our findings from these (over)complex models to the larger population of patients and stick to purely descriptive results when considering more than one explanatory covariate.

The PP analysis of de novo postoperative worsening of erectile function after vsAR and tAR will be performed as well (two-sided Fisher’s exact test at the 20% significance level) to explore the effect of full-thickness transection on postoperative erectile function.

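### The only centre-adjusted version of the primary analysis (Cox model plus exponential conversion) is unsuited to the 4 to 5 failures expected, and gives no valid limit in the 9.5% to 15% of trials where no tAR patient fails

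*Protocol article*

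**What the plan says.** The section on analysis of the primary end-point attaches the non-inferiority decision to the 80% confidence interval for the difference in 24-month failure-free survival (FFS), alongside the Kaplan-Meier curves. It notes that this ignores the nesting of patients in centres. As the remedy, "a marginal Cox proportional hazards model can be fitted" with a cluster-robust variance, and the limit for the hazard ratio "can be transformed into a limit of survival difference at 24 months, assuming an exponential distribution of failure-free survival times". The section does not say which way the hazard ratio runs, which arm's rate enters the conversion, or what status the converted limit has beside the Kaplan-Meier result.

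The section on additional analyses explains why interaction models were dropped: "the rule of thumb says that at least 10 failures are needed per degree of freedom included in the model". It then restricts itself to description for models with more than one covariate.

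The sample size section supplies the rates: "the FFS at 24 months for vsAR and tAR were 95.3% (standard deviation (SD), 2.3%) and 95.4% (SD, 2.0%) respectively".

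**The concern.** A Cox model estimates a ratio of hazards, and that needs failures in both arms. A procedure with about 95% success in 100 men leaves very few. If one arm has none, the hazard ratio has no finite estimate, and a conversion built on it has nothing sound to convert.

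This is the only method the plan names for dealing with centres, in a multi-centre trial randomised within centre. The plan itself warns that the unadjusted standard errors may be affected, so a reader may take the adjusted result as the sounder one. If it is degenerate in a realistic share of trials, it cannot serve as a check on the main result.

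**Working it through.** **Inputs, all from the protocol's sample size section.** 24-month failure 4.6% (tAR) and 4.7% (vsAR); margin 10 points; one-sided alpha 0.10; power 0.80; 50 per arm randomised. With 20% drop-out, 50 x 0.8 = 40 per arm remain evaluable.

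**Step 1. The plan's own figure.** n = (1.2816 + 0.8416)^2 x (0.954 x 0.046 + 0.953 x 0.047) / (0.10 - 0.001)^2 = 4.508 x 0.08868 / 0.009801 = 40.8, so 41. This matches "Alpha 0.10: 41 patients per arm". The rates used below are therefore those on which the plan was sized.

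**Step 2. Expected failures.** n x (0.046 + 0.047) = 4.65 at 50 per arm and 3.72 at 40. The probability of 10 or more failures in total (sum of two binomials) is 1.8% and 0.4%. The technique term alone uses one degree of freedom, so the quoted threshold is 10. Even with vsAR truly at the margin (85.4%), the expected totals are 50 x (0.046 + 0.146) = 9.6 and 40 x 0.192 = 7.7.

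**Step 3. Chance that no tAR patient fails.** 0.954^50 = 9.5%; 0.954^40 = 15.2%. Neither depends on the vsAR rate.

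**Step 4. The Cox fit in that case.** The model was fitted in R (`coxph` with `cluster()`), with 0 of 50 tAR failures, assuming 5 centres and failures found at the 3-, 12- or 24-month visit. With 1, 5, 10 and 25 vsAR failures the log hazard ratio was 20.2 to 20.6, so the upper 80% limit for the hazard ratio was of order 10^9. The model-based standard error was about 5,000 to 24,000, but the robust one only 0.5 to 1.0. The variance the plan asks for thus prints a narrow interval around a ratio that has no finite value.

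**Step 5. The conversion.** With S(t) = exp(-lambda t), the vsAR survival is the tAR survival raised to the power HR.
- Lambda from the observed tAR arm: lambda = 0, so S_tAR = 1, and 1^HR - 1 = 0 for any finite HR.
- Fixed 95.4%: 0.954^HR - 0.954, with HR near 10^9, = -0.954.
- Lambda from the vsAR arm: S_vsAR - S_vsAR^(1/HR), with 1/HR near 0, = S_vsAR - 1, the point estimate.

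For comparison, the direct Kaplan-Meier lower limit without drop-out is -p - 1.2816 x sqrt(p(1-p)/50), where p is the vsAR failure proportion. An arm without failures adds no Greenwood variance.

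| vsAR failures (tAR 0/50) | observed tAR rate | fixed 95.4% | vsAR rate | Kaplan-Meier |
|---|---|---|---|---|
| 1/50 | 0 | -0.954 | -0.02 | -0.045 |
| 3/50 | 0 | -0.954 | -0.06 | -0.103 |
| 5/50 | 0 | -0.954 | -0.10 | -0.154 |
| 10/50 | 0 | -0.954 | -0.20 | -0.272 |
| 25/50 | 0 | -0.954 | -0.50 | -0.591 |

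The first choice always passes. The second always fails, even at 1/50, where the direct limit passes. The third carries no sampling error, so at 3/50 it passes while the direct limit fails.

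**The case against.** **The Cox route is optional and decides nothing.** This stands. The decision wording belongs to the Kaplan-Meier difference. With no tAR failures that rule passes vsAR at 2/50 (-0.04 - 1.2816 x sqrt(0.04 x 0.96/50) = -0.076) and rejects it from 3/50 (-0.103). A reader might infer that the trial carries a 9-15% false-positive risk, or that vsAR passes however many of its patients fail. The document supports neither. The zero difference needs lambda from the observed tAR arm, which the plan never states, and no decision is tied to the converted limit.

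**Choice of lambda is a detail for the analysis plan.** Fair, and its absence is not the point. The point is that each of the three direct choices fails when tAR has no failures. A fourth source, the Cox model's own fitted baseline, does better: fitted vsAR survival is 0.98, 0.90, 0.80 and 0.50 for 1, 5, 10 and 25 failures. Its interval still rests on the robust standard error of a diverged ratio. With 5 vsAR failures, two random draws of centre and failure time gave 0.52 and 0.78.

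**The frequency could be overstated.** One could quote 18% to 28% for at least one arm without failures, but that includes trials where only vsAR has none, and there a favourable difference is correct. Also, at the planning rates vsAR has at most 2 failures in about 58% (50 per arm) to 71% (40 per arm) of the zero-tAR trials, and the direct rule passes those too.

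**The 10-failure rule was meant for interaction models.** Partly right. The restriction drawn from it concerns more than one covariate, and `cluster()` adds no degree of freedom, so this is not an outright contradiction. The rule as worded counts every degree of freedom, however, and the one-term model does not meet it.

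**Conclusion.** The point holds for the centre-adjusted analysis only. At the protocol's own rates it would run on 3.7 to 4.65 expected failures, with at most a 1.8% chance of reaching 10. In 9.5% to 15.2% of trials no tAR patient fails, and the converted limit is then 0, about -0.95 or the bare point estimate, according to a choice the plan does not state.

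The Kaplan-Meier rule is untouched, so no inflation of the trial's type I error is shown. What remains is that the plan's only named answer to clustering is unreliable under its own assumptions, and that nothing says which result prevails if the two differ. The percentages rest on a 95.4% tAR rate and 40 to 50 evaluable men per arm; the Cox fits assume 5 centres. This should be changed, at low cost.

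**What to change.** State that the Kaplan-Meier difference at 24 months decides non-inferiority and that the centre-adjusted result is supportive. Replace the Cox model and its conversion with a centre-adjusted estimate on the difference scale that allows for censoring. Examples are a centre-weighted difference in 24-month Kaplan-Meier FFS, or 24-month pseudo-values regressed on arm and centre with an identity link. Read its 80% lower limit against the same -10%. A plain binary Mantel-Haenszel difference would not do unadapted, because the plan censors drop-outs at their last visit and expects 20% of them.

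The cost is a few lines of text and slightly less familiar code. The new estimate exists when one arm has no failures. It remains uninformative when neither arm has any, with probability 0.954^50 x 0.953^50 = 0.9% to 0.954^40 x 0.953^40 = 2.2%.
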